**Fig. 1 Fig1:**
[figure not shown]
Depiction of serial bio-sampling and analysis performed during study conduction; pathogen testing will be performed only at first study visit (V1), while serial blood sampling will be performed repetitively at every study visit (V1–V13)

To ensure maximal safety for medical staff involved in this clinical study, SOPs for clinical sample handling are defined. Personal safety equipment for laboratory staff includes tightly closed protective gown, face shield or protective glasses, surgical face mask, and protective gloves. All blood samples are handled under a bio-safety level (BSL) 2 hoods and primary tubes are discharged. Analyses of infectious specimen will be handled according to the current regulation under BSL2 safety conditions.

#### Post-mortem analysis

Post-mortem analysis under strict safety considerations will be considered for patients succumbing to COVID-19 in this study. A detailed SOP has been devised at our institution. Autopsy will provide in-depth insights into viral tropism and organ pathologies of severe disease. Additional analysis of infected tissue using spectral confocal microscopy will provide insights into the pathology of fatal COVID-19. Samples will be stored for future analysis.

### Data management and storage

Clinical and laboratory data will be collected from patient charts, through patient interviews or from examinations and submitted online to a purpose-built eCRF using the electronic data capture system SecuTrial^®^. All data will be pseudonymized using a six-digit alphanumerical patient code and the online records kept will not include any information that allows patient identification. An enrolment log list will be used to match patient codes in the database to individual patients to record clinical outcomes and supply any missing data points. The enrolment log and study data will be kept separately. Access to the database is protected by username and password. The electronic database set up in this study is suitable for the use in interventional trials and can, therefore, rapidly be modified for future clinical testing of therapeutic agents.

### Quality assurance and control measures

A detailed data dictionary will define data to be collected on eCRF. Quality checks will be built into the data management system, including the possibility to generate queries, to ensure standardization and validity of the data collected. Any information that is not available to the investigators will be considered as missing. No assumptions will be made for missing data. Data monitoring of a randomly selected subset of collected data will be performed in the course of the study. Discussion of data collection techniques throughout the course of the study with investigators will ensure data quality and allow for adjustments.

### Data storing, access, and sharing

Access to samples for additional analyses, open access, and data sharing via the Global Research Collaboration for Infectious Disease Preparedness (GloPID-R) will be governed by a research committee comprising the clinical lead investigators and scientific investigators for this study. It is a fundamental principle of this study that all contributors and researchers who have access to samples commit to unrestricted data sharing to provide timely insights into this new disease. In addition, all clinical investigators contributing to this research efforts will be given full recognition for their efforts and the opportunity to access data and samples. Data management adheres to the FAIR data principles, stating that all data collected shall be findable, accessible, interoperable, and re-usable [26]. Samples collected will be used for the purpose of this study as stated in the protocol and consented for future use.

### Ethics and registration

This study is conducted in compliance with the principles laid down in the 1964 Declaration of Helsinki and its later amendments. Where applicable, the principles of Good Clinical Practice (International Council for Harmonization, ICH 1996) and other applicable regulations and guidelines will be used to guide procedures and considerations. The study was reviewed and approved by the Charité Ethics Committee (EA2/066/20). All patients enrolled will give written informed consent in person, or by a legal guardian. Pa-COVID-19 is registered at the German Clinical Trials Register and WHO International Clinical Trials Registry Platform (DRKS00021688).

Medical management of participants in this study must never be compromised by study procedures. At all times, priority will be given to samples required for medical management and day-to-day care of patients. Study blood samples will be taken together with routine blood sampling for clinical monitoring to minimize the individual risk connected with phlebotomy or manipulation of intravascular catheters. There is no direct benefit for patients participating in the study, but results from the study might improve clinical care in future patients and benefit public health.

Specific ethical consideration includes the recruitment of critically ill patients who might not be able to consent, the strong moral obligation to participate in a public health emergency, keeping the balance between public health and research, and the potential risk for research staff involved in this study.

The enrolment of patients, who are unable to consent, is a common challenge in critical care, acute research, and minors. The process follows a clear legal framework with consent being obtained from legal guardians as soon as possible. In addition, all efforts will be made to obtain informed consent from patients retrospectively after recovery. For patients refusing retrospective informed consent, all data and biosamples will be deleted. For patients succumbing to COVID-19 before informed consent can be obtained, all data will be anonymized.

The patient information clearly outlines potential benefits and limitations. The autonomy and well-being of the individual patient and the medically indicated procedures and treatments are always paramount. All staff is trained in infection control measures and has ready access to appropriate personal protective equipment. Dedicated research staff will be available to support the study activities.

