*The aim of Pa-COVID-19: *harmonized deep clinical, molecular, and immunological phenotyping in patients with COVID-19 to (i) elucidate the pathophysiology of the disease, (ii) identify diagnostic and prognostic scores and biomarkers for improved clinical management, (iii) identify putative therapeutic targets, (iv) produce evidence regarding short- and long-term clinical outcomes, and (v) identify correlates of protective immunity. Longitudinal data- and bio-sampling as well as post-mortem analysis will enable for characterization of clinical features of distinct disease courses and identify determinants of severity and transmission.

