### Exclusion criteria

Refusal to participate by patient, parent, or appropriate legal representative.

Any conditions that prohibit supplemental blood sampling.

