In addition to medical history and history of present illness, we aim for detailed longitudinal documentation of (i) clinical symptoms, (ii) vital signs and blood gases, (iii) laboratory parameters (including inflammation markers, cardiac enzymes, coagulation parameters, etc.), (iv) imaging data (e.g., X-ray, echocardiography, ultrasound, CT scans, and MRI scans), (v) microbiological and virological tests, (vi) supplementary diagnostic data (e.g., bronchoscopy and lumbar puncture), (vi) concomitant medication, and (vii) details of clinical interventions (mechanical ventilation, organ replacement therapy, etc.) (Table 1). Patients can also be included in Pa-COVID-19 if they participate in other clinical studies, e.g., in interventional clinical trials. In these patients, trial participation and application of any study medication will be documented in the eCRF. During in-patient stay, the patient-reported health status will be measured using tailored short forms from the Patient-Reported Outcome Measurement Information System^®^ (PROMIS), targeting for precise assessments of dyspnoea and physical function [22]. Overall outcomes will be evaluated using clinician as well as patient-reported health data, including the WHO 7 category ordinal scale [23] at study visits until day 15 and at discharge from hospital. Quality of life, health status, and performance in activities of daily living will be assessed using the Barthel Index and an adapted version of the PROMIS^®^-29 Profile at discharge, 6 weeks, 3 months, 6 months, and 12 months after inclusion. In addition, lung function, blood gases, cardiac function, renal function, occurrence of Post-Intensive Care Syndrome, neuropsychiatric function, exercise capacity, and cognitive function will be assessed in selected patient groups at follow-up visits [24].

**Table 1 Tab1:** Study procedures: each visit during the patient's hospital stay will register as a new visit

Visit	Enrolment											
	V1	V2	V3	V4	V5	V6	V7	V-discharge	V8^a^	V9^a^	V10^a^	V11^a^
Visits will be conducted three times a week until discharge from hospital^e^	Monday/Wednesday/Friday starting day of enrolment							Day of discharge	6 weeks after enrolment	3 months after enrolment	6 months after enrolment	12 months after enrolment
Visit windows	–	–	–	–	–	–		–	± 1 week	± 2 week	± 3 weeks	± 3 weeks
Informed consent/authorization	×											
Epidemiological data	×^d^											
Demographics	×^d^											

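### Among patients enrolled without their own consent, deleting survivors who later refuse while keeping those who die overstates mortality whenever any survivor refuses

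*Protocol article*

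**What the plan says.** The Ethics and registration section covers patients who cannot consent when they are enrolled. A guardian is approached first: "The process follows a clear legal framework with consent being obtained from legal guardians as soon as possible". The patient is then asked in person: "all efforts will be made to obtain informed consent from patients retrospectively after recovery".

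Two rules follow, one for each way this can end:

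- Survivors who decline: "For patients refusing retrospective informed consent, all data and biosamples will be deleted".
- Patients who die first: "For patients succumbing to COVID-19 before informed consent can be obtained, all data will be anonymized".

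A separate rule applies at entry. Under Exclusion criteria, a patient is left out on "Refusal to participate by patient, parent, or appropriate legal representative".

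The outcome data at stake include clinician and patient-reported health data, "including the WHO 7 category ordinal scale [23] at study visits until day 15 and at discharge from hospital". One aim in the Introduction is to "produce evidence regarding short- and long-term clinical outcomes"; another is to find prognostic scores and biomarkers.

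Under Data management and storage, the link between code and patient is a working tool: "An enrolment log list will be used to match patient codes in the database to individual patients to record clinical outcomes". The same sentence also uses the log to fill in missing data points.

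**The concern.** Refusal after recovery is open only to people who recover. The two rules therefore remove some survivors and no deaths at that step, and whether a patient stays in the data depends on the outcome being measured. This happens when the rules are followed exactly; it needs no departure from the protocol.

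In this subgroup the retained data would show too high a mortality, and a prognostic model fitted to them would start from too high a baseline risk. The Quality assurance section makes no assumptions for missing data, so nothing stated there would correct for patients who have been removed altogether. Recruitment has begun, and the article offers itself as a national blueprint, so other centres may copy the pair of rules.

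A second, smaller matter concerns the patients who die. If anonymization cuts their link to the enrolment log, outcomes and missing items can no longer be completed through it, and autopsy findings (planned under Post-mortem analysis) may be hard to join to the clinical record.

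**Working it through.** The article states no mortality, refusal rate or share of patients enrolled without their own consent, so there is no figure of its own to reproduce. The direction follows from the rules. The sizes below rest on assumed ranges.

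**1. Subgroup mortality.** Let *m* be true mortality among patients enrolled without their own consent, and *r* the share of survivors who refuse and are deleted. Deaths kept: *m*. Survivors kept: (1 − *m*)(1 − *r*).

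Observed mortality = *m* / [*m* + (1 − *m*)(1 − *r*)]

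This equals *m* at *r* = 0 and exceeds *m* for every *r* > 0 (with *m* between 0 and 1). Example: *m* = 0.40 and *r* = 0.10 gives 0.40 / (0.40 + 0.60 × 0.90) = 0.40 / 0.94 = 42.6%.

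| True *m* | *r* = 5% | *r* = 10% | *r* = 20% | *r* = 30% |
|---|---|---|---|---|
| 20% | 20.8% | 21.7% | 23.8% | 26.3% |
| 30% | 31.1% | 32.3% | 34.9% | 38.0% |
| 40% | 41.2% | 42.6% | 45.5% | 48.8% |
| 50% | 51.3% | 52.6% | 55.6% | 58.8% |

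The inflation is about 1 point at 5% refusal, about 2 to 3 points at 10%, and about 4 to 6 points at 20%.

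**2. Whole cohort.** Let a share *q* be enrolled this way, with assumed mortality of 40% in that share and 5% in the rest.

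True mortality = 0.40*q* + 0.05(1 − *q*); observed = true / (1 − 0.60*qr*)

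| *q* | True | *r* = 5% | *r* = 10% | *r* = 20% |
|---|---|---|---|---|
| 10% | 8.5% | 8.53% | 8.55% | 8.60% |
| 20% | 12.0% | 12.07% | 12.15% | 12.30% |
| 30% | 15.5% | 15.64% | 15.78% | 16.08% |

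Even at *q* = 30% and *r* = 30%, the result is 0.155 / 0.946 = 16.4%, a shift of 0.9 points.

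**3. Mean severity.** Take 100 patients on a 7-point scale with 7 assumed to be death: 40 deaths, 20 survivors at 6, 40 survivors at 3. The true mean is (280 + 120 + 120) / 100 = 5.20. Delete 6 survivors:

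- in proportion (2 at 6, 4 at 3): mean 5.28
- all from the milder group: mean 5.34
- all from the sicker group: mean 5.15

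The share of deaths is 40/94 = 42.6% in all three cases, but the mean can rise or fall.

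**4. Guardian refusal at entry.** If guardians refuse equally often for later survivors and later deaths, the factor cancels and the bias in step 1 stands in full. If refusal fell only on patients who later die, then at *m* = 40% and *r* = 10% a guardian refusal share of 10% gives 0.36 / (0.36 + 0.54) = 40.0%, and 20% gives 0.32 / (0.32 + 0.54) = 37.2%.

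**5. Effect of adding the deleted survivors back.** In the example in step 3, a count of 6 turns 40/94 = 42.6% into 40/(94 + 6) = 40.0%. The count alone is enough to undo the bias from this step.

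**The case against.** The strongest reply is that deletion on refusal is an ethics-approved safeguard, and that a condensed article may leave participant-flow counts and sensitivity analyses to the full protocol or the analysis plan. Both parts are fair. The deletion rule is not in dispute, and the absence of a stated count is not an error in itself. What stands is that the article does state a pair of rules, and that pair selects on survival.

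Guardian refusal could pull the other way. It offsets the bias only if it falls more heavily on patients who later die. The outcome is unknown at entry, and nothing in the document suggests such a pattern. It is a separate selection step.

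The article also does not say outright that anonymized records enter the outcome analyses. That they do is the natural reading, but it is a reading.

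Four stronger inferences are tempting and are not supported:

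- **Severity is biased upward as well.** Step 3 shows that this depends on which survivors refuse.
- **All critically ill patients are affected.** Only those enrolled without their own consent are.
- **The size of the bias can never be recovered.** No text says that no count is kept; this would be inferred from silence.
- **An analysis that excludes patients who died without any consent would test the problem.** It selects on death. With 40 deaths and 60 survivors, and half the deaths assumed to lack any consent, it gives 20/80 = 25.0%, or 20/74 = 27.0% after 6 survivors are deleted. That is 13 to 15 points too low, as a check on a bias of 2.6 points.

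**Conclusion.** The point holds for mortality in patients enrolled without their own consent. At the retrospective-consent step only survivors can be removed, so mortality there is overstated whenever at least one survivor refuses, and unaffected if none does. The direction rests on reading anonymized as retained and on guardian refusal at entry not falling mainly on later deaths.

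The size cannot be known from the article. It is modest at low refusal and reaches several points in the subgroup if a fifth of survivors refuse; in the cohort as a whole it stays small under every combination tried. This does not threaten the study, but it bears on the group in whom mortality and prognosis matter most, and it is cheap to correct if arranged before deletions take place.

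**What to change.** - Keep the deletion rule unchanged.
- Before each deletion, add one to an aggregate count of survivors who refused retrospective consent. Keep it coarse: at a single hospital, cross-classifying refusers by several features could leave very small cells. Obtain ethics committee confirmation that such a count may be kept.
- Report the count. Report mortality in this subgroup and in the cohort with the deleted survivors added back to the denominator, beside the uncorrected figure.
- Describe prognostic results as conditional on consent. A count cannot restore the deleted patients' covariates.
- Complete outcome entry and the linkage of samples and autopsy findings for patients who die before their data are anonymized, because the enrolment log is the stated means of recording outcomes and filling gaps.

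The cost is one query to the ethics committee, one running count and a little extra reporting. No additional patient data are retained.

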## Conclusion

This study protocol of the observational prospective cohort study Pa-COVID-19 that has recently started recruitment at Charite - Universitätsmedizin Berlin may serve as a blueprint for data and biosample collection in patients with COVID-19 in Germany. The protocol combines a comprehensive clinical and translational approach with tools for implementation in different clinical settings. It is scalable to local resources, and by design, this platform allows for rapid initiation of interventional trials, which are urgently needed to investigate effective treatments for COVID-19.

## Data Availability

The study protocol shall serve as a blueprint for studies conducted on patients infected with SARS-CoV-2 in Germany.
